### **Data analysis and evaluation of results**

STATA (StataCorp LP, College Station, Texas) will be used for the analysis.

#### **1. Develop benchmark data for inappropriate medication use that can be compared across hospitals in Quebec and Canada.**

We will provide a descriptive summary of the population enrolled in this study including participant age, gender, comorbidities, type of prescription, other prescriptions, length of stay, residence type, and the number who enrolled in deprescription. (i.e., Table 1).

#### **2. Evaluate the effectiveness of a hospital-based deprescription intervention for unnecessary gabapentinoid prescriptions.**

Participants will be grouped by control and intervention based on the timing of the study. The primary outcome will be the complete cessation of gabapentinoid use or intent to taper to discontinuation (prescribed taper) measured at 8-weeks post hospital discharge. A secondary outcome will be measured as a dose reduction, without any intent to taper to discontinuation (decrease in medication use after

exposure to the intervention but no taper to complete cessation prescribed at the time of the 8-week study follow-up period).

### Statistical analysis plan

We will use an "intention to treat" principle. We will analyze participant data according to their participation during the intervention or control period. For the primary outcome, we will perform a sensitivity analysis for patients who died or were lost to follow-up using the most recent available data on their gabapentinoid use (inpatient pharmacy records, discharge prescriptions or the provincial electronic medical record). We will assess binary outcomes using binomial regression comparing the intervention to no intervention and adjusting for age and sex. We will assess continuous outcomes (T scores) using linear regression comparing the intervention to no intervention, adjusting for baseline values, age and sex.

We will perform several preplanned subgroup analyses for the primary outcome, including an analysis of participants aged 80 or older; analyses based on reason for admission, discharge destination (community v. long-term care facility) and comorbidities; and an analysis looking at the effect of each study unit. Subgroup analyses will be treated as hypothesis generating and presented graphically with 95% confidence intervals.

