## Research design and methodology

This will be a prospective controlled before and after study involving two centres: the McGill University Health Centre (MUHC) Glen Site (Royal Victoria Hospital) and the Montreal General Hospital. The control and intervention units will be the five medical units.

The study will begin in the control period. Based on previous study data regarding the prevalence of admitted gabapentinoid users and the average number of monthly admissions on the clinical teaching units, recruitment in the control period should last approximately 12 months. All study sites will simultaneously transition to the intervention period after 80 patients have been recruited (estimated 1 year). The rationale for simultaneous transition of all units is to reduce the risk of inter-site contamination of the intervention, as it is common for medical residents and staff to work in all the study sites during a given year. The decision to transition to the intervention period after 80 patients have been recruited is motivated by the need to reduce the risk of bias introduced by temporal trends in deprescribing secondary to level of training of junior residents and seasonal variations of workload on the medical wards. If the target number of control participants is reached before the 12-month mark, recruitment will be suspended until then. The intervention period will be completed once the pre-specified target number of 80 intervention participants is reached, which is expected to take approximately 12 months as well.

Follow up of discharged patients will be at 8 weeks post-discharge. We will analyze and publish the results afterwards.

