### Controls

All units will serve as their own controls during the initial control period. During this period, participants admitted to the medical ward with gabapentinoid use pre-admission (which are referred to as "gabapentinoid users") will receive usual medical care (pharmacy medication reconciliation). Although they will be informed that the goal of the trial is to evaluate medications and changes post discharge, they will be unaware that gabapentinoids are specifically targeted, so as to reduce the risk of contamination of the control arm. Furthermore, the medical staff will not receive specific information about the trial, or particular instructions with regards to deprescription during the control period.

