## **Data collection**

Information about participants will be collected by the research assistants from the participants and their medical record. We will abstract reason for admission, comorbidities and other medications from the chart. At time of enrollment, we will obtain consent to directly obtain prescription history from the *Dossier Santé Québec* (DSQ), which is a prescription record database for all patients in Québec, as well as from the community pharmacy from which participants receive their medications. These will serve to validate deprescription. During the index admission, a first questionnaire will be administered in person and will collect information about demographics, including age, gender and residence style (independent, assisted living, etc.). We will also obtain a medication use history (for study drugs) and standardized questionnaires to assess global functioning, pain control and cognition. Follow up questionnaires will be administered at 8 weeks after hospital discharge by telephone. The follow-up questionnaire will collect any demographic changes such as destination of discharge and length of stay, will ask participants about deprescription (cessation, reduced use, intent to reduce, or no change), initiation or dose increase of other pain medications, occurrence of withdrawal symptoms, and finally will repeat the global functioning, pain control and cognition questionnaires.

Death will be determined from hospital records. Participants who are known to have died before 8 weeks post-discharge will be excluded from the analysis of the primary outcome (as they cannot attain it); however, they will be retained in the study for descriptive purposes and other outcomes.

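### The primary model adjusts only for age and sex, so a shift in unit mix or case mix between the two non-randomised periods would bias the period effect.

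*Protocol*

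**What the plan says.** - **Design.** Under Research design and methodology, "The control and intervention units will be the five medical units". Under Controls, "All units will serve as their own controls during the initial control period".
- **Allocation.** Under Data analysis, item 2, "Participants will be grouped by control and intervention based on the timing of the study". The switch depends on an overall count: "All study sites will simultaneously transition to the intervention period after 80 patients have been recruited (estimated 1 year"). No section sets a target per unit.
- **Primary model.** The Statistical analysis plan section states: "We will assess binary outcomes using binomial regression comparing the intervention to no intervention and adjusting for age and sex".
- **Where unit appears.** Only in the preplanned subgroup list, as "an analysis looking at the effect of each study unit". Reason for admission, discharge destination and comorbidities are in the same list. Of all these, "Subgroup analyses will be treated as hypothesis generating and presented graphically with 95% confidence intervals".
- **What is collected.** Under Data collection, "We will abstract reason for admission, comorbidities and other medications from the chart". The same section adds residence type and a use history for the study drugs.

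**The concern.** The two groups are different patients recruited in different years. Nothing in the recruitment rule keeps each unit's share, or the kind of patient, the same in both periods. Age and sex capture part of any difference in patients and do not stand in for unit.

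Using the same five units in both periods protects the comparison only if the analysis compares like with like inside units. The stated model pools all patients, so a change in unit shares passes into the period effect. The same holds for any other baseline characteristic that predicts deprescribing and changes in frequency. The Protocol treats unit, comorbidities and reason for admission as worth examining in subgroups, yet leaves them out of the estimate on which the trial will be judged.

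The section on other sources of bias discusses trends over time and answers with earlier retrospective data and the spacing of the periods. It does not address a change in mix. Because the Protocol names the covariates, this is not a detail deferred to a separate plan.

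**Working it through.** **1. The Protocol's own figure.** Inputs from Justification of sample size: 13% in the control period, a 20-point increase (so 33%), two-sided 5% error, 80% power, 15% loss. The pooled-variance formula for two proportions gives 69 per group. Allowing for loss gives 69/0.85 = 82, or 69 × 1.15 = 80. The stated 80 per group reproduces and is not in dispute. After 15% loss, 80 × 0.85 = 68 per group are evaluable, with power 79.8%. Expected events: 68 × 0.13 + 68 × 0.33 = 31.

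**2. Bias from unit mix.** With no true effect, bias = sum over units of (unit rate × change in that unit's share). The Protocol gives neither quantity, so both are assumptions. Rates are evenly spaced around 13%, shares start at 20% each, and recruitment moves from the lowest-rate to the highest-rate unit:

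| Assumed unit rates | 10 points move | 20 points move |
|---|---|---|
| 9 to 17% | 0.10 × 8 = 0.8 points | 0.20 × 8 = 1.6 points |
| 5 to 21% | 0.10 × 16 = 1.6 points | 0.20 × 16 = 3.2 points |
| 3 to 23% | 0.10 × 20 = 2.0 points | 0.20 × 20 = 4.0 points |

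Moving recruitment the other way reverses the sign.

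**3. Effect on the test.** With 68 per group and no true effect, a two-sided 5% test rejects in 5.8% of trials at 1.6 points of bias, 8.2% at 3.2 points and 10.0% at 4.0 points.

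**4. Bias from case mix.** The same formula applies to a binary baseline variable. If deprescribing differs by 20 to 30 points between its levels (assumed) and its prevalence shifts by 20 points (assumed), the bias is 0.20 × 20 = 4 to 0.20 × 30 = 6 points. Smaller values give less: a 10-point difference and a 10-point shift give 1 point.

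**5. Does a unit term help?** A simulation used unit rates of 5 to 21%, 68 per group and three mix shifts of 10 to about 20 points, with a risk-difference regression fitted with and without unit indicators.
- No true effect (1,500 runs each): mean estimate 1.9 to 3.3 points without unit, −0.1 to 0.4 with unit.
- True effect of 20 points (600 runs each): mean 21.2 to 23.1 without unit, 19.5 to 20.0 with unit.
- No mix shift: power 80% without unit and 81% with it.
- Mix shift present: power with unit was 73 to 75%. The 83 to 90% without unit is inflated by the bias.

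**6. Standard error.** There are 68/5 = 13.6 evaluable patients per unit and period. With ICC for the intracluster correlation and r for the between-period correlation as a share of it, design effect = 1 + (13.6 − 1) × ICC − 13.6 × ICC × r. ICC and r are assumptions.

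| ICC | r = 0.8 | r = 0.5 |
|---|---|---|
| 0.01 | 1.02 (power 79%) | 1.06 (power 78%) |
| 0.02 | 1.03 (power 78%) | 1.12 (power 75%) |
| 0.05 | 1.09 (power 76%) | 1.29 (power 69%) |

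The design effect falls below 1 once r exceeds 12.6/13.6 = 0.93.

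**The case against.** **Size.** Bias needs two things at once: a shift in mix, and units or patient types that differ in deprescribing. The Protocol documents neither. It expects about 50 admissions a month on each unit and says staff and residents rotate across sites, which argues for even shares and similar practice. This stands, and it is why the size is given as a range under assumptions. A reader might infer that mix shifts will be read as benefit, or could produce the 20-point effect. The documents do not support either: the direction is unknown, and unit mix alone gives at most about 4 points here.

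**Precision.** A reader might infer that ignoring units makes the standard error too small and cuts power to 69%. That is conditional. Each unit contributes to both periods, so stable unit differences cancel, and above r = 0.93 the simple error is conservative. The 69% is the worst cell of an assumed table. Fixed unit terms would not correct this component either, because they absorb only the stable part.

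**Design rationale.** The Protocol justifies the before-after design by avoiding contamination, and its statement that units are their own controls does not promise a unit-matched estimator. That is fair. The point rests on non-randomised periods and a fixed covariate list, not on a broken promise.

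**Already visible.** Unit, comorbidity and admission-reason subgroups, plus the descriptive table, will show the mix. True, but displaying it does not adjust the primary estimate.

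**Parsimony.** With about 31 events a small model is defensible. This limits the number of added covariates; it does not argue against unit.

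**Conclusion.** The point holds in a conditional form. The primary model leaves measured unit-mix and case-mix differences in the estimate of a non-randomised comparison. The resulting bias can go either way. It is about 1 to 4 points (0.8 to 4.0) from unit mix under assumed rates averaging 13% and assumed shifts of 10 to 20 points, and of similar order from case mix under further assumptions. That would not manufacture the target effect, but it could distort the estimate and tip a borderline result.

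The standard error may be too small only if unit rates vary between periods, with a design effect of about 1.02 to 1.29 for assumed ICC 0.01 to 0.05 and between-period correlation 0.5 to 0.8. It would be wrong to infer that adjustment makes the comparison safe: there is no concurrent control, so a time trend shared by all units remains whatever is added to the model. The change is worth making because it is cheap.

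**What to change.** - Add unit to the primary binomial model as a fixed term with five strata, and report the marginally standardised risk difference. Five units are too few for reliable random-effect or cluster-robust inference.
- Keep age and sex, and pre-list a short set of baseline variables from data already collected, for example comorbidity count, opioid or sedative co-use, and baseline gabapentinoid dose. With about 31 expected events, keep the list few or carry it through a period-propensity weight. Choose one route in advance.
- As a sensitivity analysis for unit-by-period variation, report the paired comparison of the five unit-level period differences. It has only 4 degrees of freedom, so its interval will be wide.
- State in the plan that adjustment cannot remove a secular trend common to all units.

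Cost: some wording and coding, no new data, and a few degrees of freedom. In the simulation the unit term cost essentially no power when the mix was stable. When the mix shifted, power was 73 to 75%, in exchange for removing most of the bias.

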## **Justification of sample size**

The estimated sample size is 160 participants, with 80 in the control group and 80 in the intervention group. The sample size was calculated to detect an absolute increase of 20% in deprescription rates with the intervention (number needed to treat 5), allowing for a two-sided type 1 error of 5% and a type 2 error of 20%. Based on the results of a previous retrospective descriptive study of gabapentinoid prescriptions in medical inpatients, the control period event rate (discontinuation) is expected to be 13% [8]. The expected loss to follow-up is approximately 15%, including deaths.

There are approximately 50 patients admitted per month on each clinical teaching unit (total 200 admissions across the study units), of which 13% are expected to be taking gabapentinoids prior to admission [8]. Approximately 75% of admitted gabapentinoid users are aged 60 years and older. Assuming a refusal rate of 15%, as seen in the EMPOWER study [26], we expect a maximum of 16 participants enrolled per month.

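### The age and unit subgroup plan names no comparison between subgroups, and with about 14 patients per unit per period the unit results will usually look different by chance alone

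*Protocol*

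**What the plan says.** The protocol's section Statistical analysis plan lists preplanned subgroup analyses of the primary outcome. For age the list reads "including an analysis of participants aged 80 or older", and the 60-79 group is not mentioned. For wards it reads "an analysis looking at the effect of each study unit". Reason for admission and comorbidities are also listed, as is discharge destination, for which both sides are named. On reporting: "Subgroup analyses will be treated as hypothesis generating and presented graphically with 95% confidence intervals".

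The only model the section gives for binary outcomes is binomial regression on period, adjusted for age and sex. The link is not stated, so the effect could be a ratio or a difference. No interaction or heterogeneity estimate is mentioned, and none is ruled out.

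On size, Justification of sample size says "The estimated sample size is 160 participants, with 80 in the control group and 80 in the intervention group" and "The expected loss to follow-up is approximately 15%, including deaths". It takes a 13% control rate and a 20-point absolute increase. Research design and methodology gives five medical units.

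**The concern.** A subgroup question asks whether the effect differs between groups. An estimate in those aged 80 or older, shown alone, cannot answer it, because nothing stands beside it for comparison.

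The unit analysis has a different difficulty. The units act as their own controls, and this is the only planned look at whether the effect is consistent across them. Spread over five units, the trial leaves so few control-period events in each that the stated model may fail there, and the estimates will scatter widely even when the true effect is the same everywhere. A plot of unit intervals with no summary of heterogeneity invites the conclusion that the brochure works on some wards and not on others.

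**Working it through.** **Inputs.** From Justification of sample size: 80 per period, 13% control rate, 33% under intervention (13% + 20 points), two-sided 5% error, 80% power, 15% loss including deaths. From Research design and methodology: five units. Assumed: equal unit sizes and the planned rates in every unit.

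**Reproducing the sample size.** With the pooled-variance formula, mean rate (0.13 + 0.33)/2 = 0.23:

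n = [1.96 × √(2 × 0.23 × 0.77) + 0.842 × √(0.13 × 0.87 + 0.33 × 0.67)]² / 0.20² = 68.3, so 69 per group.

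Allowing for loss, 69 × 1.15 = 79.4 (80), or 69/0.85 = 81.2 (82). The stated 80 is reproduced. Evaluable per period: 80 × 0.85 = 68.

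**Events per unit.** 68/5 = 13.6 patients per unit per period. Expected events: 13.6 × 0.13 = 1.8 control and 13.6 × 0.33 = 4.5 intervention, about 6.3 in total. The adjusted model has four parameters (intercept, period, age, sex).

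**Units with no control event.** For one unit the chance is 0.87^m; for at least one of k units it is 1 − (1 − 0.87^m)^k.

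| Units | Evaluable controls | m | One given unit | At least one unit |
|---|---|---|---|---|
| 5 | 68 | 13.6 | 15% | 56% |
| 5 | 80 (no loss) | 16 | 11% | 43% |
| 4 | 68 | 17 | 9% | 33% |
| 4 | 80 (no loss) | 20 | 6% | 22% |

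If the 68 controls fall at random across five units instead of equally, the 56% becomes 61%. The four-unit rows are there because the sample size section's own admission figures, 200 per month in total and 50 per unit, give 200/50 = 4, which conflicts with five. In a unit with no control event a risk ratio or odds ratio cannot be estimated; a risk difference can.

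**Fitting the adjusted model within one unit.** Simulated with 14 v 14 patients, ages uniform from 60 to 95 and half women (both assumed), 1,000 data sets per link, run twice. No usable estimate (no convergence, a fitted probability outside 0 to 1, or a diverging coefficient) was obtained in about 15-18% of fits with a logit link, 32-38% with a log link and 74-76% with an identity link. The rates depend on software and on the failure rule, but no link is dependable here.

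**Same effect in every unit.** 200,000 simulated trials, 13% v 33% in each of five units, 14 per period per unit, Newcombe 95% intervals for the risk difference:

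- Some unit intervals exclude zero and others do not: 74%. None excludes zero: 26%. All five do: under 0.1%.
- Mean half-width of a unit interval: 29 points.
- At least one unit with a zero or negative difference: 53%.
- Median gap between highest and lowest unit estimate: 36 points.
- With four units of 17 per period, the mixed picture occurs in 71%.

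**A direct comparison on the same data.** With d_j the risk difference in unit j, d̄ their mean, and p_C and p_I the control and intervention proportions pooled over units, Q = Σ(d_j − d̄)² / {[p_C(1 − p_C) + p_I(1 − p_I)]/m}, referred to chi-square on k − 1 degrees of freedom. It rejects in 5.0% of trials, as it should under a uniform effect, and it needs no non-zero cell in any unit.

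**Age.** The protocol gives no share aged 80 or older; 30% to 50% is assumed. That is 68 × 0.3 = 20 to 68 × 0.5 = 34 patients per period, with power of 32% to 50% for the full planned effect in that group. With the same effect on both sides, the two age intervals disagree about excluding zero in 50% to 54% of trials, while an interaction test rejects in about 6%.

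**The case against.** The strongest reply is that the protocol states no wrong method. A plot with 95% intervals is an ordinary forest plot. Nothing says that models will be fitted separately, that an interval excluding zero will be taken to mean the intervention works there, or that an interaction term will not be used. Naming such a term is often left to a separate analysis plan, which may exist. The phrase on study units could mean a unit term in the full model. This stands: a reader might infer that subgroups are to be judged by comparing separate intervals, but the text is silent, and the 74% figure measures what happens only if they are read that way.

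A reader might also infer that the unit estimates are largely uncomputable. That goes too far. Only a ratio is undefined when a unit has no control event, the link is not fixed, and the sample size is framed as an absolute difference, which is always defined. On a ratio scale about 15% of individual units are affected; the 56% is the chance that at least one of five is.

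Three further points stand. The one-sided criticism applies to age and not to discharge destination. The label of hypothesis generation limits the harm. And unadjusted unit intervals, which are recommended below, would scatter just as much.

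What the reply does not remove is that this section does fix an 80-or-older analysis without its counterpart and an effect for each unit, alongside a model that is unreliable within a unit. The exploratory label limits what may be claimed, but it does not make the display able to answer the question.

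**Conclusion.** The point holds as a minor improvement to the wording. Followed literally, the plan cannot show whether the effect differs by age or by unit, and it would usually display unit differences that are noise: about 74% of trials under a uniform effect with five units, 71% with four. The adjusted model should not be relied on within a unit of about 14 patients per period.

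These sizes rest on equal units, the planned 13% and 33% in every unit, and the full 15% loss; the age figures also rest on an assumed share aged 80 or older. The conclusion is the same for four or five units. The primary analysis and its sample size are untouched.

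**What to change.** In the protocol's Statistical analysis plan:

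- Report participants aged 80 or older and those aged 60-79 together, and show every category of the other subgroups.
- For each subgroup factor, give a period-by-subgroup interaction estimate with its 95% CI from one full-sample model.
- For units, show unadjusted risk differences with Newcombe intervals plus one period-by-unit heterogeneity estimate on the difference scale, and do not fit the adjusted model unit by unit.
- State that consistency across units will be judged by the heterogeneity estimate and not by which unit intervals exclude zero.

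The cost is a few sentences, with no new data and no change to the sample size. The downside is that the interaction and heterogeneity estimates will be imprecise, so absence of a detected difference will not demonstrate consistency; the report should say so.
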